### Study endpoints

The primary endpoint is wound area reduction after 4 weeks of treatment with APO-2, i.e., wound area at visit 14 (end of treatment visit) compared to visit 2 (randomization). Secondary endpoints are > 50% reduction in wound area after 4 weeks (binary outcome); wound size at baseline and 1, 2, 3, 4, 6, 8, and 12 weeks after the first application of IMP; proportion of patients with complete wound closure during the 12-week follow-up period (100% re-epithelialization of the wound surface with the absence of drainage); time to complete wound closure; recurrence rate of the ulcer during the 12-week follow-up period; clinical assessment of peripheral neuropathy at baseline, 4, and 12 weeks after the first application of IMP; number of patients with local adverse events or serious adverse events (SAEs) with causal relationship to study medication; evaluation of wound pain by visual analogue scale (VAS) at baseline, at every treatment visit, and 4, 6, 8, and 12 weeks after the first application of IMP; and evaluation of quality of life using Wound QoL questionnaire at baseline, 4, and 12 weeks after the first application of IMP.

Patients who discontinue the trial prematurely after having received at least one dose of IMP will be regarded as “early termination,” and the circumstances and reasons of their discontinuation must be documented in the eCRF. All effort should be done to follow-up with the patient visit schedule as per protocol, but at least a complete end-of-treatment examination should be performed.

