### Sample size calculation and power

Sample size calculation for the primary efficacy endpoint is based on the assumptions that after 4 weeks, a wound area reduction of 45%, 50%, and 55% (at a dose of 12.5 U/ml, 25 U/ml, and 50 U/ml, respectively) can be achieved compared to 40% reduction in the placebo group (significance level = 0.05 (two-sided); power = 80%).

Based on estimated wound reductions for each group, a variance of mean of 0.003 was calculated. A standard deviation within groups is estimated 0.156 based on previous studies and expert opinion. The calculated minimal number of patients per group is 23, calculated with Nquery Advisor® (STATCON GmbH, Witzenhausen, Germany) [30].

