### Statistical analysis

For the preceding safety lead-in part of the study, safety data of 12 randomized patients will be summarized after the 4-week treatment period. These data will be evaluated by the DSMB. Unblinding is not planned but is possible if requested by the DSMB. Safety and efficacy results of the safety lead-in phase will be included in the data pool of the entire clinical study for final analysis (i.e., the safety lead-in phase is an integral part of the entire MARSYAS II study).

The main study is designed to evaluate the dose-response relationship for clinical efficacy of topical APO-2 at three dose levels compared to placebo. The minimum effective dose, which is defined as the smallest dose with a discernible, useful effect, will be determined.

The primary endpoint is the assessment of the dose-related, relative reduction in wound area from baseline to week 4 (continuous endpoint). Analysis of the primary and secondary efficacy variables will be based on the full analysis set (i.e., all patients with a measured wound size at baseline, who received at least one dose of IMP and have data available at the end of treatment visit). Details are defined in a statistical analysis plan. If data are normally distributed, one-way analysis of variance (ANOVA) will be calculated, including a Dunnett multiple comparison post hoc test, to test each of the active doses against placebo. If Gaussian distribution is not given, a non-parametric Kruskal-Wallis test with Dunns post hoc tests will be performed. If at least one of the doses is statistically significant, then the dose-response relationship is established. In addition, a dose-response model will be developed and tested. Three candidate models (linear, quadratic, and logistic) will be fitted to the data and the Akaike Information Criterion will be used to select the best model. Confidence bands for the estimated dose-response curve will be presented. Binary endpoints will be analyzed by displaying the number and percentage of patients in each dose group. Differences among dose groups will be tested using Fisher’s exact test. For the evaluation of the continuous endpoints, data will be analyzed as absolute values and changes from baseline will be represented by basic statistics (mean, standard deviation, minimum, first quartile, median, third quartile, maximum). A detailed description of the reports and tests is specified in a statistical analysis plan.

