For the primary endpoint, the last observation carried forward (LOCF) procedure will be applied. If the visit 14 measurement of wound size is missing, the last available post-baseline measurement will be used.

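### The article's rules do not settle how a patient who leaves at week 1–2 without a day-30 wound image is analysed: dropped, or scored with an early area as the 4-week result

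*Protocol article*

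**What the plan says.** Four places in the protocol article bear on this.

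- **Study endpoints, primary endpoint:** "wound area at visit 14 (end of treatment visit) compared to visit 2 (randomization". The Statistical analysis section describes the same quantity as the relative reduction from baseline to week 4.
- **Table 3 (visit schedule):** visit 14 carries the end-of-treatment label and is set at day 30 ± 5, that is day 25 to 35. The table has no separate early-termination visit. Wound size is measured at every visit, including visits 3 to 13.
- **Study endpoints, early termination:** for patients who stop after at least one dose, "All effort should be done to follow-up with the patient visit schedule as per protocol", "but at least a complete end-of-treatment examination should be performed".
- **Statistical analysis:** the full analysis set consists of patients with a baseline wound size "who received at least one dose of IMP and have data available at the end of treatment visit". The missing-data rule, given separately, is: "If the visit 14 measurement of wound size is missing, the last available post-baseline measurement will be used".

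**The concern.** One term serves three purposes: the minimum examination for early leavers, the primary time point, and the condition for entering the primary analysis. Nothing in the article separates an exit examination at week 1 or 2 from visit 14. The analysis-set condition and the LOCF rule also pull against each other. The first removes patients without end-of-treatment data, and the second is written for patients whose visit 14 area is missing.

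At stake is the comparison of each dose with placebo. An area taken after one or two weeks understates what a still-shrinking wound would show at week 4, so an arm with more or earlier stops looks less effective. If the patient is dropped instead, the analysis loses a randomised and treated patient for a reason that arises after randomisation. The direction of any resulting bias cannot then be predicted.

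**Working it through.** **1. The possible routes for a patient who stops at day 7 or 14.** These days lie 25 − 7 = 18 and 25 − 14 = 11 days before the visit 14 window opens.

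| Route | In the full analysis set? | Value used for week 4 |
|---|---|---|
| A. Exit exam counts as the end-of-treatment visit | Yes | Early area, as an observed value |
| B1. Exam does not count; analysis-set condition read literally | No | None |
| B2. Exam does not count; LOCF applied | Yes | The same early area, carried forward |
| C. Visits continue to day 30 | Yes | A real day-30 area |

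Route C is the article's stated preference and raises no problem. Without a day-30 image, the text does not choose between A, B1 and B2. A and B2 give the same number and differ only in whether it is recorded as observed or imputed.

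**2. The plan's own sample size.** Inputs from the Sample size section: mean reductions of 40%, 45%, 50% and 55%; within-group SD 0.156; two-sided 5% level; 80% power; 23 per group. For a four-group one-way ANOVA the noncentrality is λ = n·4·V/SD².

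- The variance of the four means is V = 0.003125. With n = 23, λ = 23 × 4 × 0.003125 / 0.024336 = 11.8 on 3 and 88 df, and power is 81.5%.
- With the article's rounded V = 0.003, power is 79.8% at n = 23.

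The stated 23 per group is reproduced. The planned high-versus-placebo difference is 55 − 40 = 15 points.

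**3. Illustration of the early-area routes (A and B2).** The article gives no healing curve or dropout rate, so both are assumed. With log-linear healing, the reduction at day d is 1 − (1 − m)^(d/28).

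| Trajectory m | Day 7 score | Day 14 score | Shortfall at day 7 / day 14 |
|---|---|---|---|
| 55% (high dose) | 1 − 0.45^0.25 = 18.1% | 1 − 0.45^0.5 = 32.9% | 36.9 / 22.1 points |
| 40% (placebo) | 1 − 0.60^0.25 = 12.0% | 1 − 0.60^0.5 = 22.5% | 28.0 / 17.5 points |

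If the total of 132 includes the 12 lead-in patients, the main study has (132 − 12)/4 = 30 per arm.

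- *Three of 30 stop, high-dose arm only:* the arm mean falls by 0.1 × 36.9 = 3.7 points (day 7) or 0.1 × 22.1 = 2.2 points (day 14). That is 25% or 15% of the 15-point difference.
- *10% stop in both arms:* the difference shrinks by 3.69 − 2.80 = 0.9 points (day 7) or 2.21 − 1.75 = 0.5 points (day 14).

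**4. A second healing shape.** With linear healing, a 40% trajectory scores 10% at week 1 and 20% at week 2. Suppose there is no true effect (40% in both arms) and 15% stop in one arm against 5% in the other. The false difference is then 0.10 × (40 − 10) = 3 points or 0.10 × (40 − 20) = 2 points, in favour of the arm with fewer stops. The direction agrees with step 3.

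**5. The exclusion route (B1).** No shift can be calculated, because it depends on how leavers differ from completers, and the article says nothing on that. The loss of numbers can be shown: 10% exclusion takes 23 per group to 20, where power under the plan's assumptions is 75.0%.

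**The case against.** The strongest reply has five parts.

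- **The exit-exam reading is an inference.** A reader might infer that the examination takes place on the day of leaving and is entered as visit 14, so that every early stopper supplies an early area as observed week-4 data. The article does not say so. It puts continued visits first, gives no timing for the fallback examination, and schedules visit 14 at day 30 ± 5. The sentence can equally mean that at least the scheduled visit 14 should be kept. This stands, and it makes the point an unresolved ambiguity.
- **The label does not change the number.** If the exam is not visit 14, LOCF carries the same area forward. This also stands. The label decides only whether the patient is in the analysis set and whether the value is marked as imputed. Using an early area as the week-4 result is already an open rule of the plan.
- **The distortion is not concealed.** Early-termination patients are documented with reasons in the eCRF, and a blinded data review precedes database lock. They can be identified.
- **The size is easily overstated.** Dividing the 2.2–3.7 points by the 5-point step between adjacent doses would give 44–74%. The planned Dunnett tests compare each dose with placebo, so for stops in the high-dose arm the relevant difference is 15 points. The illustration also assumes that a patient who stops at day 7 would otherwise reach the full 55%, which may be too generous.
- **Visit mapping belongs in the SAP.** A missing mapping rule alone would be no finding. But the article itself states both the analysis-set condition and the LOCF rule, and for this patient they lead to different outcomes. They could be reconciled by confining LOCF to patients who attend visit 14 without a usable wound measurement. A week 1–2 leaver with no visit 14 is then excluded, and the article does not state that restriction.

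**Conclusion.** The point holds in this form: for a patient who leaves at week 1–2 without a day-30 image, Table 3, Study endpoints and Statistical analysis do not settle whether the patient is excluded or analysed with an early area as the 4-week value. Each available route can bias the dose comparison when stopping differs between arms.

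The size is not known. Under assumed log-linear healing, one-sided stopping of 3 in 30 in the high-dose arm shifts its mean by 2.2–3.7 points out of 15, and equal 10% stopping narrows the difference by about 0.5–0.9 points. The shift scales with the share that stops. The documents do not support the stronger conclusion that early areas will routinely pass as week-4 results because of the visit name. Scheduled follow-up is preferred, and LOCF would give the same value without the shared name.

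**What to change.** Reconcile the three sections with four changes.

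1. Label any examination before day 25 as an early-termination visit, and state that it is not visit 14 and does not supply the week-4 value.
2. Remove the end-of-treatment-data condition from the full analysis set, so that treated patients with a baseline area and at least one post-baseline area stay in.
3. For every patient who stops treatment, seek the already scheduled day-30 wound image and use it in the primary analysis.
4. Where that image is missing, estimate week 4 from all measured areas with a repeated-measures model as the primary approach, with the dose-versus-placebo comparisons taken at week 4. Keep LOCF as a sensitivity analysis.

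The cost is protocol and SAP wording and one eCRF visit label. No new visit is needed, and wound areas are already collected at the treatment visits. The planned ANOVA and its non-parametric alternative would have to be restated to fit the model. The downside is small: a few week-4 values rest on a model and its missing-at-random assumption, and the LOCF sensitivity analysis shows how far the result depends on how they are handled.

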### Sample size calculation and power

Sample size calculation for the primary efficacy endpoint is based on the assumptions that after 4 weeks, a wound area reduction of 45%, 50%, and 55% (at a dose of 12.5 U/ml, 25 U/ml, and 50 U/ml, respectively) can be achieved compared to 40% reduction in the placebo group (significance level = 0.05 (two-sided); power = 80%).

Based on estimated wound reductions for each group, a variance of mean of 0.003 was calculated. A standard deviation within groups is estimated 0.156 based on previous studies and expert opinion. The calculated minimal number of patients per group is 23, calculated with Nquery Advisor® (STATCON GmbH, Witzenhausen, Germany) [30].

### Statistical analysis

For the preceding safety lead-in part of the study, safety data of 12 randomized patients will be summarized after the 4-week treatment period. These data will be evaluated by the DSMB. Unblinding is not planned but is possible if requested by the DSMB. Safety and efficacy results of the safety lead-in phase will be included in the data pool of the entire clinical study for final analysis (i.e., the safety lead-in phase is an integral part of the entire MARSYAS II study).

The main study is designed to evaluate the dose-response relationship for clinical efficacy of topical APO-2 at three dose levels compared to placebo. The minimum effective dose, which is defined as the smallest dose with a discernible, useful effect, will be determined.

The primary endpoint is the assessment of the dose-related, relative reduction in wound area from baseline to week 4 (continuous endpoint). Analysis of the primary and secondary efficacy variables will be based on the full analysis set (i.e., all patients with a measured wound size at baseline, who received at least one dose of IMP and have data available at the end of treatment visit). Details are defined in a statistical analysis plan. If data are normally distributed, one-way analysis of variance (ANOVA) will be calculated, including a Dunnett multiple comparison post hoc test, to test each of the active doses against placebo. If Gaussian distribution is not given, a non-parametric Kruskal-Wallis test with Dunns post hoc tests will be performed. If at least one of the doses is statistically significant, then the dose-response relationship is established. In addition, a dose-response model will be developed and tested. Three candidate models (linear, quadratic, and logistic) will be fitted to the data and the Akaike Information Criterion will be used to select the best model. Confidence bands for the estimated dose-response curve will be presented. Binary endpoints will be analyzed by displaying the number and percentage of patients in each dose group. Differences among dose groups will be tested using Fisher’s exact test. For the evaluation of the continuous endpoints, data will be analyzed as absolute values and changes from baseline will be represented by basic statistics (mean, standard deviation, minimum, first quartile, median, third quartile, maximum). A detailed description of the reports and tests is specified in a statistical analysis plan.

For the primary endpoint, the last observation carried forward (LOCF) procedure will be applied. If the visit 14 measurement of wound size is missing, the last available post-baseline measurement will be used.

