**Fig. 1 Fig1:**
[figure not shown]
Study design of the MARSYAS II study

**Table 1 Tab1:** Partners in the safety lead-in phase of the MARSYAS II study

Sponsor	Aposcience AG
CRO	FGK Clinical Research GmbH
Service provider for IMP storage and distribution	ABF Pharmaceutical Services GmbH
Drug manufacturer	Austrian Red Cross, Blood Transfusion Service for Upper Austria
Safety lead-in	
Study center 1	Kepler Universitaetsklinikum Linz
Study center 2	A.oe. Krankenhaus der Elisabethinen Klagenfurt
Backup study center 1	Fakultní nemocnice u sv. Anny, Brno
Backup study center 2	Fakultní nemocnice Královské Vinohrady, Prague
Backup study center 3	Ústřední vojenská nemocnice - Vojenská fakultní nemocnice, Prague

The study design is based on the results and experiences of the clinical study MARSYAS I, where the topical application of autologous APOSEC was tested in healthy volunteers. The study MARSYAS II is divided into a main study phase (phase IIa, parallel group, four-arm, exploratory trial with equal allocation ratio and superiority testing for secondary endpoints) and a safety lead-in phase (phase I, parallel group, two-arm, exploratory trial with 3:1 allocation ratio) which precedes the main phase and evaluates the safety of the IMP. In the safety lead-in phase, only the medium dose is administered. Between screening and randomization visit, a run-in time period of a minimum of 2 weeks is implemented to observe if the wounds heal when treated with standard of care (SoC) and to include only patients with impaired wound healing.

After the run-in period, the treatment period starts and lasts for 4 weeks, followed by an 8-week follow-up period without application of IMP but with continuation of treatment with SoC.

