**Assessments**							
**Physical examination and vital signs**	X	X		X			X
**Hematology**^a^	X						X
**Serum chemistry**^b^	X						X
**Urine analysis**^c^	X						X
**Urine pregnancy test**	X	X		X			
**Wound assessment**	X	X	X	X	X	X	X
**Assessment of wound closure**	X	X	X	X	X	X	X
**Wound size measurement (eKare inSight®)**	X	X	X	X	X	X	X
**Standard of care for wound management**	X	X	X	X	X	X	X
**VAS—score for pain**	X	X	X	X	X	X	X
**Neurological assessment foot**		X		X			X
**Chronic wound quality of life questionnaire**		X		X			X
**Recording adverse events**		X	X	X	X	X	X

^a^Erythrocytes/leucocytes/hemoglobin, hematocrit, thrombocytes, MCV, MCH, and MCHC

^b^Sodium, potassium, total protein, albumin, BUN, creatinine, glucose, Hba1c, AST, ALT, GGT, total bilirubin, and CRP

^c^Urine dip stick: pH, nitrite, glucose, leucocyte, ketone, bilirubin, protein, and blood

In the safety lead-in period, a minimum of 12 patients will be enrolled and randomly assigned (3 active: 1 placebo) to receive the medium dose of APO-2, (25 U/ml, 9 patients) or placebo (3 patients). Randomization is done by computer-generated random numbers, and the information is only given to the pharmacist who prepares the IMP. Safety assessments of patients in the safety lead-in period will include recording of adverse events (AEs), use of concomitant medications, and wound size measurement. Immediately after the last randomized patient reaches the end of treatment with IMP, safety and efficacy data of the safety lead-in period will be reviewed by an independent Data and Safety Monitoring Board (DSMB). During this evaluation, study enrollment will be paused and only the active patients will be followed up. The DSMB board consists of three independent experts in the field of clinical wound care and one statistician.

After a review of the safety results, the DSMB will make a recommendation as to whether or not the main study may start as designed (i.e., randomized, double-blind, parallel group). The DSMB may also recommend the inclusion of additional patients in the safety lead-in period prior to initiation of the main study. After the DSMB decision, the patients in the safety lead-in period will continue to be followed as per protocol completing the 8-week follow-up period after the last administration of the investigational product. Besides the DSMB, no other interim analyses or formal stopping rules are intended.

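### Pooling the lead-in (medium dose and placebo only) into a one-way primary analysis partially confounds study phase with dose and can distort the dose-response shape

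*Protocol article*

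**What the plan says.** The two phases have different designs. In the text after Table 1 (Study setting), the lead-in is a "phase I, parallel group, two-arm, exploratory trial with 3:1 allocation ratio", and "In the safety lead-in phase, only the medium dose is administered". Standard study procedures gives the numbers: at least 12 patients, "randomly assigned (3 active: 1 placebo) to receive the medium dose of APO-2, (25 U/ml, 9 patients) or placebo (3 patients"). The main study has four arms in equal ratio.

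The phases also differ in place, time and stratification:
- Table 1 lists two Austrian lead-in centres and three Czech backup centres. The whole study selected 16 sites in four countries (Study setting).
- The first lead-in patient was enrolled in autumn 2020. Enrolment pauses for review by the Data and Safety Monitoring Board (DSMB), and the main study is planned from Q2 2021 (Standard study procedures; Trial status).
- Stratification by wound size is described for the main study only.
- The DSMB may ask for more lead-in patients.

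The Statistical analysis section then combines the phases: "Safety and efficacy results of the safety lead-in phase will be included in the data pool of the entire clinical study for final analysis". For the primary endpoint it names the test: "one-way analysis of variance (ANOVA) will be calculated", with Dunnett comparisons of every active dose with placebo. Where the data are not normal, "a non-parametric Kruskal-Wallis test with Dunns post hoc tests will be performed". It also plans linear, quadratic and logistic dose-response fits, chosen by the Akaike Information Criterion (AIC), and determination of a minimum effective dose.

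**The concern.** A one-way ANOVA has dose group as its only factor, and Kruskal-Wallis has no stratum. Patients were randomised within each phase, not across phases. Low- and high-dose patients have no concurrent lead-in counterparts, and the medium arm takes three lead-in patients for every one that placebo takes. If lead-in patients heal differently on average, because of site, period or case mix, part of that difference appears in the pooled dose contrasts.

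The primary objective is the dose-response relationship. A phase difference raises or lowers the middle dose relative to its neighbours, which can create or hide curvature, influence the AIC choice and shift the minimum effective dose.

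**Working it through.** **Plan's own figure.** The Sample size section assumes reductions of 40%, 45%, 50% and 55% and a within-group SD of 0.156. The mean is 0.475, so the variance of means is (0.075² + 0.025² + 0.025² + 0.075²)/4 = 0.0125/4 = 0.003125, printed as 0.003. With 23 per group, the noncentrality is 4 × 23 × 0.003125/0.156² = 11.8 and the F-test power is 81.5%. The stated 23 per group reproduces and is not affected by this point.

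**Pooled arm sizes (assumption: 132 includes the 12 lead-in patients).** The main study then has (132 - 12)/4 = 30 per arm.

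| Arm | Main | Lead-in | Pooled | Lead-in share |
|---|---|---|---|---|
| Placebo | 30 | 3 | 33 | 3/33 = 0.091 |
| Low | 30 | 0 | 30 | 0 |
| Medium | 30 | 9 | 39 | 9/39 = 0.231 |
| High | 30 | 0 | 30 | 0 |

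**Bias.** For an unadjusted contrast, bias = phase shift × difference in lead-in share.
- Medium versus placebo: 0.231 - 0.091 = +0.140
- Low or high versus placebo: 0 - 0.091 = -0.091
- High versus medium: 0 - 0.231 = -0.231

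The documents give no phase shift, so every shift below is assumed. Results are in percentage points of wound area reduction.

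| Assumed shift | Medium vs placebo | Low or high vs placebo | High vs medium |
|---|---|---|---|
| 5 | +0.7 | -0.45 | -1.2 |
| 10 | +1.4 | -0.9 | -2.3 |
| 20 | +2.8 | -1.8 | -4.6 |

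**Dose ordering.** The SE of high minus medium is 0.156 × √(1/39 + 1/30) = 3.79 points. Under the planned 5-point step, the chance that the observed medium mean exceeds the high mean is Φ(-5/3.79) = 9% with no shift, Φ(-(5 - 2.31)/3.79) = 24% at +10 points and Φ(-(5 - 4.62)/3.79) = 46% at +20.

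**Type I error.** In simulation with no drug effect, SD 0.156 and the shift added to the lead-in patients themselves, familywise Dunnett error is about 5.0% with no shift and 5.2%, 5.9% and 8.3% at 5, 10 and 20 points. Separate runs at 20 points ranged from 7.9% to 8.3%.

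**Power under the planned effects.** For the medium dose it is about 63% with no shift, about 74% at +10 points and about 46% at -10. For the high dose it falls from 92% to 88% at +10.

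**Other sizes.** The coefficients, in the order medium-placebo, low or high-placebo, high-medium:
- 132 excludes the lead-in (33 per main arm): +0.131, -0.083, -0.214
- 23 per main arm plus 12: +0.166, -0.115, -0.281
- Lead-in doubled at the same 3:1 ratio (30 per main arm plus 24): +0.208, -0.167, -0.375, with Dunnett error of about 8.3% at a 10-point shift

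**The case against.** The strongest reply has four parts.

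**A large phase shift is neither documented nor especially likely.** The article gives one set of eligibility criteria, one run-in stability rule, one visit schedule, one standard of care and one centrally adjudicated wound measurement for both phases. The endpoint is a relative reduction, which partly offsets differences in baseline size. Twenty points exceeds the whole planned range from placebo to high dose (55 - 40 = 15 points). This stands, and it is why every magnitude here is conditional.

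**The effect is small beside sampling error.** At a 10-point shift, the 1.4-point bias in medium versus placebo compares with an SE of 3.69 points. This also stands. The larger 2.3- and 4.6-point figures concern high versus medium, which Dunnett does not test. They bear on the fitted curve.

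**Details are left to a statistical analysis plan that is not shown.** This stands only in part. Sensitivity analyses may well be there, and their absence from the article is not criticised. But the article itself fixes both the pooling and a one-way test. A plan that put phase in the primary model would depart from that test.

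**Stronger readings go too far.** A reader might infer that phase is wholly confounded with dose. It is not: placebo and medium dose occur in both phases, so a phase effect is estimable. A reader might also infer that the 5% error rate is lost. That holds only if a shift exists, and the inflation is modest. Moving the arm means while keeping the error SD at 0.156 gives about 6.4% and 11% at 10 and 20 points, but this overstates it, because the extra spread within the pooled arms enters the ANOVA error term.

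**Conclusion.** The point holds as partial confounding. The stated pooling and the stated one-way analysis together leave the pooled contrasts not fully protected by randomisation. The bias coefficients of +0.14, -0.09 and -0.23 rest on the assumption that 132 includes the lead-in, and change little if it does not. The bias in points rests wholly on an assumed phase shift. The case for change lies in the dose-response shape, the AIC selection and the minimum effective dose more than in type I error, and it grows if the DSMB enlarges the lead-in. Since both phases are labelled exploratory and only 12 of about 132 patients are involved, this is a should-fix point.

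**What to change.** Settle one of two options before unblinding.

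1. **Adjust for phase.** Add phase (lead-in or main) as a fixed factor in the ANOVA/Dunnett model and in each dose-response fit. Lead-in patients then inform only the medium-placebo comparison within their own phase. This removes an additive phase shift and costs one degree of freedom. The SE of medium versus placebo rises from 3.69 to 3.76 points (+1.8%), and of low or high versus placebo from 3.94 to 3.96 (+0.7%). Kruskal-Wallis cannot take a phase term, so that branch needs a phase-stratified rank test or restriction to main-study patients.

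2. **Make main-study patients the primary set** and the pooled set a sensitivity analysis. This covers both branches and does not rely on the shift being additive. With 30 per arm, each SE against placebo is 0.156 × √(2/30) = 4.03 points: 4.03/3.69 = 1.09, so 9% more for medium, and 4.03/3.94 = 1.02, so 2% more for low or high.

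Either option needs only a change of wording in the protocol and analysis plan, and no new data. The text should also say whether 132 includes the lead-in.

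### The full analysis set requires end-of-treatment data, so most patients the LOCF rule is meant for are excluded before it can apply

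*Protocol article*

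**What the plan says.** In the protocol article, Statistical analysis: "Analysis of the primary and secondary efficacy variables will be based on the full analysis set". Members of that set need a measured wound size at baseline and are patients "who received at least one dose of IMP and have data available at the end of treatment visit".

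Study endpoints identifies the end of treatment visit with the primary endpoint visit: "wound area at visit 14 (end of treatment visit) compared to visit 2 (randomization". Table 3 places it at day 30, plus or minus 5 days.

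The missing-data rule closes the Statistical analysis section: "For the primary endpoint, the last observation carried forward (LOCF) procedure will be applied". It continues: "If the visit 14 measurement of wound size is missing, the last available post-baseline measurement will be used". No such rule is given for the secondary endpoints.

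For patients who discontinue after at least one dose, Study endpoints asks that they be kept on the visit schedule as far as possible, "but at least a complete end-of-treatment examination should be performed". It does not say whether an examination done early counts as visit 14.

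**The concern.** The two rules conflict for the patients who matter most to a missing-data rule. LOCF is there for someone whose visit 14 wound size is absent. The commonest such person is one who left before visit 14 and has no data from it, and the analysis-set definition has already removed that person.

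The consequence goes beyond wording. Membership of the set depends on something that happens after randomisation. If patients are lost because the ulcer worsened or the treatment was not tolerated, and this happens more in some arms than others, the arms compared are no longer those that were randomised. The Dunnett or Dunn comparisons with placebo and the dose-response model would all be fitted to the selected patients.

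The same set governs the secondary efficacy endpoints. Time to complete closure, closure during the 12 weeks, and wound size at weeks 1 to 3 do not need a visit 14 value. Yet a patient lost on day 20, say, is removed from these rather than contributing the time observed.

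**Working it through.** **1. The plan's own sample size.** Inputs from Sample size calculation and power: "a wound area reduction of 45%, 50%, and 55" percent in the active arms, which "can be achieved compared to 40% reduction in the placebo group"; within-group SD 0.156; two-sided alpha 0.05; power 80%.

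- Mean of the four reductions: (0.40 + 0.45 + 0.50 + 0.55)/4 = 0.475.
- Variance of means: (0.075² + 0.025² + 0.025² + 0.075²)/4 = 0.003125, given as 0.003.
- Noncentrality at 23 per group: 92 × 0.003125/0.156² = 11.8.
- Power from the noncentral F distribution with 3 and 88 degrees of freedom: 81.5%.

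The stated 23 per group reproduces. With the rounded 0.003, power at 23 is 79.8% and 24 are needed, a trivial difference. The sample size is not at fault.

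**2. The two rules side by side.**

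| Patient (baseline wound size, at least one dose) | In the full analysis set? | LOCF triggered? |
|---|---|---|
| Visit 14 wound size present | Yes | No |
| Seen at visit 14, no usable wound size | Yes | Yes |
| Left early, no end-of-treatment examination | No | Would be, but already excluded |
| Left early, end-of-treatment examination done early | Not stated | Not stated |

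Only the second row is clearly served by both rules. It is a real case: Table 3 schedules pain, neurological, quality-of-life and other assessments at visit 14, so a patient can have data there without a usable image.

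**3. Effect on power.** Assume (132 − 12)/4 = 30 per main-phase arm, ignoring the lead-in patients who will be pooled. The share without end-of-treatment data is also assumed. Variance of means is 0.003125.

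| Share excluded | Left per arm | Power |
|---|---|---|
| 0% | 30 | 91.5% |
| 10% | 27 | 88.0% |
| 20% | 24 | 83.4% |
| 23% | 23 | 81.5% |
| 30% | 21 | 77.3% |

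Power holds at 80% or more up to about 23% exclusion, so lost power is not the main issue.

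**4. Effect on the comparison.** Let μ be the true mean reduction in an arm, d the share without end-of-treatment data and r their mean reduction. The mean in those analysed is (μ − d·r)/(1 − d). Take μ = 0.40 in both arms, so that there is no true effect, and r = 0. All values of d and r are assumptions.

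| d, placebo | d, active | Placebo mean | Active mean | Apparent difference |
|---|---|---|---|---|
| 10% | 10% | 44.4% | 44.4% | 0 |
| 20% | 10% | 50.0% | 44.4% | −5.6 points |
| 20% | 5% | 50.0% | 42.1% | −7.9 points |
| 10% | 20% | 44.4% | 50.0% | +5.6 points |

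The planned step between adjacent doses is 5 points. Equal loss of the same kind of patient leaves no bias in the difference.

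**5. What LOCF does once it can act.** At the plan's placebo figure, 40% in 28 days, and an assumed constant healing rate, a patient whose last measurement is on day 14 is credited with 1 − 0.60^(14/28) = 22.5%. Letting LOCF act settles who is analysed. It does not by itself give an unbiased week-4 value, which is why a sensitivity analysis is needed.

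**The case against.** The strongest reply is that the rules do not strictly contradict each other. The set definition asks only for data at the end of treatment visit, whereas LOCF is triggered by a missing wound size. A patient seen at visit 14 without a usable reading satisfies both. This stands: LOCF has a narrow use, not an empty one.

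A reader might also infer that the primary analysis is confined to patients who complete treatment. The documents do not support that. Early terminators are to be followed on schedule, or at least given an end-of-treatment examination, and those with such data may well qualify. Stopping treatment for infection or intolerance does not by itself exclude anyone. Nor does the text say that an area measured at two weeks would be analysed as a week-4 value; it is silent.

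It can further be said that the bias figures rest wholly on assumed dropout, that the trial is exploratory with only four weeks of treatment, and that details are deferred to a statistical analysis plan that is not shown. The first is correct. The other two limit the consequences but do not cure the conflict, because both rules are fixed in this document and an analysis plan cannot honour both for a patient who left without visit 14 data.

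Finally, replacing the primary analysis with a mixed model would go further than the defect requires. It assumes data missing at random and would have to be squared with the planned Dunnett comparisons and the non-parametric fallback.

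**Conclusion.** The point holds as a defect in the definition of the analysis set. As written, treated and randomised patients without end-of-treatment data are dropped from the primary and all secondary efficacy analyses, and LOCF reaches only those with other visit 14 data but no usable wound size. This rests on the text alone.

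Whether bias results depends on whether loss is related to dose or healing. The documents give no dropout rate and no outcomes for lost patients, so neither size nor direction is known. Under the assumptions shown, the spurious difference ranges from −7.9 to +5.6 points, including zero when loss is alike in both arms. Those figures show only that moderate unequal loss could match the planned 5-point step; they are not estimates for this trial. The sample size of 23 per group is unaffected.

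**What to change.** - Delete the end-of-treatment condition from the full analysis set, leaving all randomised patients with a baseline wound size and at least one dose. The stated missing-data rule then covers those without visit 14 data.
- State whether an early end-of-treatment examination counts as the visit 14 value or as a carried-forward value. If it is the last measurement, the number entered in the primary analysis is the same either way, but the answer decides who is in the supportive analysis below.
- Add one sentence for patients with no post-baseline wound size, for whom LOCF has nothing to carry forward.
- Keep LOCF as the stated rule and add, as a sensitivity analysis, a repeated-measures analysis of the wound areas collected at each visit.
- Report the analysis restricted to patients with visit 14 data as supportive only.

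The cost is a change of wording and a little more programming, to be settled before unblinding. No new data are needed, since Table 3 already schedules wound size measurement at every visit.
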